### Criterion for progression to a definitive randomized controlled trial

The decision to proceed with a future definitive randomized controlled trial will depend on meeting the established criteria for each feasibility outcome as shown in Table 5.

### Data management

All participant data will be kept strictly confidential. Qualitative interview data will be digitally recorded, transcribed, and de-identified after verification for accuracy. Quantitative data (e.g., survey responses, chart reviews) will be entered into an SPSS dataset without identifiable information. Each participant will be assigned a unique study ID, with identifiable information (e.g., name, contact details) stored separately from research data. Identifiable information will be maintained in a password-protected Microsoft Excel file on a secure server until study completion, accessible only to authorized research personnel. Protected health information from chart reviews will be stored separately from participant identifiers after data entry into a secure, password-protected database. Both electronic and physical copies of protected health information will use study IDs. Hard copies of data will be kept in locked file cabinets within a secured office. Electronic data will be stored in a password-protected database. Audio recordings will be erased after transcription.

### Data analysis

#### Quantitative analysis

All quantitative data analyses (e.g., descriptive statistics, correlations, and linear mixed-effects models) will be conducted using SPSS v24 and RStudio software. To assess the intervention’s potential impact on dyad outcomes, we will perform within-group, longitudinal analyses following an intention-to-treat approach. Changes in outcomes from baseline to 6-week and 12-week follow-up will be examined using linear mixed-effects models to account for repeated measures. A change of 0.3 standard deviation units or greater in key outcome measures will be considered indicative of potential efficacy, consistent with effect sizes observed in similar palliative care pilot studies. Because the nature of the study is exploratory, analysis will focus on in-sample effect size estimation rather than formal hypothesis testing. Statistical power is not a primary concern as no inferential statements will be made, which is consistent with appropriate analytical approaches for pilot study data. To analyze the acceptability and feasibility of the protocol, as well as barriers to recruitment and retention, we will use analytic techniques for mixed methods study such as content analyses and descriptive methods.

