### Objectives

To assess the feasibility and acceptability of the proposed CEDART intervention to participants.To test the feasibility and acceptability of a future definitive trial.

The main hypotheses of the study are:

The community health worker interventionist will adhere to the intervention protocol with a score of 70% or higher on the intervention fidelity checklist throughout the delivery period.Caregiver ratings of our intervention will show that the community health worker interventionist was helpful and satisfactory at the end of the intervention period.The intervention will be feasible, as evidenced by intervention completion rates greater than or equal to 70%. Completion will be defined by the proportion of participants who complete follow-up sessions and complete assessments at baseline, 6-week, and 12-week time points.Patient and caregiver outcomes will show improvement over time, as indicated by positive trends in follow-up data at 6 and 12 weeks compared to baseline.

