### Control group

This study will employ a single-arm feasibility design without a control group.

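### A 0.3 SD pre-post change without a control group is labelled potential efficacy, though it cannot be told apart from change that would follow discharge anyway

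*Protocol article*

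**What the plan says.** The Quantitative analysis section plans within-group longitudinal analyses: "Changes in outcomes from baseline to 6-week and 12-week follow-up will be examined using linear mixed-effects models to account for repeated measures". It then gives a rule for reading the result: "A change of 0.3 standard deviation units or greater in key outcome measures will be considered indicative of potential efficacy", described as "consistent with effect sizes observed in similar palliative care pilot studies". The same paragraph calls the work exploratory and says that "no inferential statements will be made".

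The Control group section confirms a "single-arm feasibility design without a control group". The Design section recruits dyads while the patient is hospitalized, and Table 1 schedules the scales first at enrollment and again at later time points.

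Hypothesis 4 under Objectives reads: "Patient and caregiver outcomes will show improvement over time, as indicated by positive trends in follow-up data at 6 and 12 weeks compared to baseline".

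The rule does not list the key outcome measures. Table 5 names QoL-AD, COPE and ZBI-4 as primary outcomes for sample-size purposes. The section on main trial outcome measurements lists these and FCAT among the secondary measures. Table 5, which governs progression to the randomized trial, contains no 0.3 SD criterion.

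**The concern.** To call a result a sign of potential efficacy is to say something about cause. A single-arm change from baseline estimates the intervention effect plus whatever would have happened over the same 6 or 12 weeks without it. Here the baseline falls around an acute admission, so there is good reason to expect the second part not to be zero. Its size is unknown, and the design cannot estimate it.

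The rule also acts on a point estimate alone. With about 40 dyads, that estimate carries an uncertainty of the same order as the threshold.

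At stake is what the trial may conclude. Potential or preliminary efficacy is a stated output in the Design, Feasibility study outcomes and Discussion sections, and a threshold crossing would be reported under that name.

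**Working it through.** The plan gives no power, alpha or operating characteristics for the rule, so there is no figure to reproduce. The check asks how often the rule is met when the intervention does nothing.

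**Inputs**
- From the protocol: threshold 0.3 SD; 40 dyads (Sample size); follow-up at 6 and 12 weeks; attrition below 30% (Table 5). At 30% attrition, 28 of 40 dyads remain, which is just outside that limit and serves as a lower bound.
- Assumed, because the documents do not give them: baseline-to-follow-up correlation r = 0.3, 0.5 or 0.7; standardisation by the baseline SD; correlation between scales 0 to 0.5; natural drift of 0.1 to 0.3 SD.

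**Precision**

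SE of the mean change in SD units = √(2(1 − r)/n); 95% half-width = 1.96 × SE.

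| n | r | SE | 95% half-width |
|---|---|---|---|
| 40 | 0.3 | 0.187 | 0.37 |
| 40 | 0.5 | 0.158 | 0.31 |
| 40 | 0.7 | 0.122 | 0.24 |
| 28 | 0.5 | 0.189 | 0.37 |

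At n=40 and r=0.5, an observed 0.30 SD has an interval of −0.01 to 0.61, which just includes zero. The half-width equals 0.30 when 2(1 − r) = 40 × (0.3/1.96)² = 0.937, that is at r ≈ 0.53. Above that correlation, an observed 0.30 SD would exclude zero.

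**Chance alone, one outcome at one visit, favourable direction**

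P = 1 − Φ(0.3/SE). At n=40 and r=0.5: 0.3/0.158 = 1.90, so P = 2.9%. For r=0.3 and 0.7 it is 5.4% and 0.7%. At n=28 and r=0.5 it is 5.6%.

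**Chance alone, any of four scales (QoL-AD, ZBI-4, COPE, FCAT) at either visit**

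Multivariate normal simulation, favourable direction, n=40, over between-scale correlations 0.5 to 0:
- r=0.5: 15–19%
- r=0.3: 26–33%
- r=0.7: 4–5%

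With only the three Table 5 scales and r=0.5, it is 13–15%.

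**Natural drift, no intervention effect, one outcome at one visit**

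P = 1 − Φ((0.3 − drift)/SE). At n=40 and r=0.5:
- drift 0.1: (0.3 − 0.1)/0.158 = 1.26, P = 10%
- drift 0.2: 0.1/0.158 = 0.63, P = 26% (30% at r=0.3, 21% at r=0.7)
- drift 0.3: P = 50%, whatever n or r

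The last line matters most: more dyads do not help, because the difficulty is bias and not noise. It also works the other way. If outcomes would decline by 0.2 SD without help and CEDART truly added 0.3 SD, the net change would be 0.1 SD, and the rule would be met only 10% of the time.

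**The case against.** A fair defence has several parts.

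**The study disclaims inference and the rule drives nothing.** This largely stands. The section on progression criteria refers to Table 5, which has no efficacy criterion, and the stated sample-size input is baseline scores and variability. A reader might infer that a false signal would decide progression or set the effect size for the randomized trial; the documents do not say so. The disclaimer does not, however, remove a sentence that tells the reader how to interpret a threshold crossing.

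**The rule is directed.** Its sentence states no sign, and a reader might infer that a 0.3 SD worsening also counts. Hypothesis 4 specifies improvement, and efficacy implies benefit, so that reading is not supported.

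**Chance rarely meets the rule.** True for one outcome at one visit. The higher figures need an any-scale, any-visit reading, which the wording leaves open but does not state.

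**Hypothesis 4 does not contradict the rule.** Correct. A positive trend and a 0.3 SD benchmark are graded descriptions: a 0.1 SD gain is a positive trend below the benchmark.

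**The baseline may not be a low point.** Table 1 places it at enrollment of hospitalized dyads but does not say that every interview takes place during the stay. Eligibility does not select on burden or quality of life, which weakens a regression-to-the-mean argument. The Background and Discussion describe transitions and the period after discharge as risky, so drift could be unfavourable. All this stands against any claim that the rule must be biased upward. It does not rescue the rule, because drift of unknown sign and size is equally inseparable from an effect.

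**Standardiser and intervals may sit in a fuller document.** Accepted. Their absence from the article is not the point here.

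**Conclusion.** The concern holds in limited form. The design cannot support the label that the protocol attaches to a 0.3 SD change, because change due to CEDART and change after discharge are not separable in one arm. If natural recovery were 0.2 to 0.3 SD, an inert intervention would earn the label about 26% to 50% of the time per outcome and visit. The rule is also imprecise at n=40: the half-width is 0.31 SD at r=0.5, so an observed 0.30 SD is compatible with no change at correlations up to about 0.53, but not at 0.7. The correlations and drift sizes are assumptions; the absence of a comparator is stated in the protocol.

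Chance alone is secondary: about 3% (1–5% over the correlations examined) for one outcome at one visit, rising to 15–19% at r=0.5 only if any of four scales at either visit may count.

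Severity is moderate. The error lies in what may be concluded about preliminary efficacy, not in the feasibility aims or the progression decision.

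**What to change.** 1. Delete the sentence that reads a 0.3 SD change as a sign of potential efficacy, or keep 0.3 SD only as a descriptive reference value.
2. For QoL-AD, COPE and ZBI-4, and for the other scales, report the mean change to 6 weeks and to 12 weeks in baseline-SD units, signed so that positive means benefit, with a 95% confidence interval.
3. Describe these results as uncontrolled within-group change, not attributable to CEDART.
4. Reword hypothesis 4 in the same descriptive terms.

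The estimates and intervals come from the mixed models already planned, so no extra data or dyads are needed. The cost is a few sentences of text and a less favourable headline on preliminary efficacy.

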### Feasibility study outcomes

Primary study outcomes will be focused on feasibility, acceptability, and fidelity. Secondary study outcomes include assessing the acceptability of measurement tools administered during caregiver interviews at baseline, 6-weeks, and 12-weeks, and exploring the preliminary efficacy of the intervention.

Main outcomes for our study focus on feasibility and include:

Number of participants with dementia and caregivers screened, eligible, and enrolled.Identification of effective recruitment strategy to inform a future definitive trial.Feasibility and acceptability of the intervention, including its content, delivery, and fidelity.Completion rates of follow-up interviews and outcome measures.Reasons for non-recruitment and attrition.Acceptability of recruitment procedures, assessments, data collection tools, and intervention delivery.Baseline scores and variability of secondary outcomes to inform sample size estimates for a future trial.

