### Sample size

As this is a single-arm pilot study, a power analysis was not required. It is suggested that sample sizes for pilot studies be determined based on practical factors such as participant availability, budget constraints, and the number of participants required to sufficiently assess feasibility outcomes [47]. Based on these considerations, a target sample size of 40 caregiver-patient dyads was selected. This sample size accounts for the estimated number of weekly admissions of patients with dementia at the recruiting hospital and the anticipated recruitment timeline.

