## Discussion

Despite evidence that persons with dementia face increased risks of morbidity and mortality after hospital discharge [51], few interventions have been designed to support hospital-based care transitions for this population [9]. Existing interventions often rely on complex protocols involving multiple modes of support [13, 52]. CEDART addresses this gap by utilizing community health workers to deliver a straightforward, replicable intervention for family caregivers of persons with dementia during hospital-to-community transition. This study will assess its feasibility, acceptability, and preliminary efficacy. If feasibility is demonstrated, findings will inform the development of a future randomized controlled trial.

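### A point estimate of 0.3 SD is labelled as potential efficacy in a paragraph that disclaims inference and attaches no measure of uncertainty

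*Protocol article*

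**What the plan says.** The Quantitative analysis section plans linear mixed-effects models for change from baseline to 6 and 12 weeks. It says that "analysis will focus on in-sample effect size estimation rather than formal hypothesis testing" and gives as its reason: "Statistical power is not a primary concern as no inferential statements will be made".

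The same paragraph sets a mark on the estimate: "A change of 0.3 standard deviation units or greater in key outcome measures will be considered indicative of potential efficacy". No interval or other measure of precision accompanies that mark.

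Other sections carry the efficacy language further:
- The Objectives section lists improvement at 6 and 12 weeks among the main hypotheses.
- The Design section expects preliminary data on potential efficacy.
- The Feasibility study outcomes section includes, as a secondary purpose, "exploring the preliminary efficacy of the intervention".
- The Discussion states: "This study will assess its feasibility, acceptability, and preliminary efficacy".

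On size, the Sample size section says that "a target sample size of 40 caregiver-patient dyads was selected" on practical grounds and that "As this is a single-arm pilot study, a power analysis was not required".

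**The concern.** Calling a change indicative of potential efficacy says something about what the intervention may do for dyads outside the sample. That is an inferential statement, however hedged, and it sits in the paragraph that says none will be made.

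Choosing estimation over testing is sound in a pilot. But estimation earns its place by showing how precise the estimate is, and low power is a reason to show precision rather than to set it aside. If the 0.3 SD mark is applied to the point estimate alone, it works as an undeclared test, and the reader cannot tell a well-determined change from one that sampling error could produce. At stake is how the preliminary-efficacy result is reported and read.

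**Working it through.** **Nothing to reproduce.** The protocol gives no power, alpha, confidence level or precision figure. The check is how precise an estimate at the 0.3 SD mark would be.

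**Inputs from the protocol**
- Full sample: n = 40 dyads (Sample size section).
- Mark: observed change of 0.3 SD (Quantitative analysis section).
- Attrition: Table 5 requires less than 30%. Losing 12 of 40 is exactly 30% and fails; losing 11 of 40 is 27.5% and passes. The fewest completers allowed are 40 - 11 = 29.

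**Assumptions (not in the protocol)**
- Two-sided 95% interval.
- Equal SDs at baseline and follow-up, with baseline to follow-up correlation r taken as 0.3, 0.5 and 0.7.
- Complete pairs at one visit, as an approximation to the mixed model.

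**Formula.** In baseline-SD units, the SD of change is sqrt(2(1 - r)), the standard error is sqrt(2(1 - r)/n), and the interval is 0.3 ± t(0.975, n - 1) × SE.

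**Worked case, n = 40 and r = 0.5.** SD of change = sqrt(2 × 0.5) = 1.000. SE = 1/sqrt(40) = 0.158. The half-width is 0.320, so the interval is 0.300 - 0.320 = -0.02 to 0.300 + 0.320 = 0.62.

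| n | r | SE | Half-width | 95% CI at an observed 0.3 SD |
|---|---|---|---|---|
| 40 | 0.3 | 0.187 | 0.378 | -0.08 to 0.68 |
| 40 | 0.5 | 0.158 | 0.320 | -0.02 to 0.62 |
| 40 | 0.7 | 0.122 | 0.248 | 0.05 to 0.55 |
| 29 | 0.3 | 0.220 | 0.450 | -0.15 to 0.75 |
| 29 | 0.5 | 0.186 | 0.380 | -0.08 to 0.68 |
| 29 | 0.7 | 0.144 | 0.295 | 0.005 to 0.595 |

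The protocol does not say which SD defines the unit. If it is the SD of change, the intervals equal those in the r = 0.5 rows.

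**Where zero enters.** The lower limit is zero when the SD of change is 0.3 × sqrt(n)/t. That is 0.938 at n = 40 and 0.789 at n = 29. Setting r = 1 - (SD of change)²/2 gives:
- n = 40: 1 - 0.938²/2 = 0.56
- n = 29: 1 - 0.789²/2 = 0.69

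Below these correlations, an estimate exactly at the mark has an interval that includes zero. Above them it does not.

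**The case against.** **Silence on intervals is not a plan to omit them.** The paragraph contrasts effect sizes with formal testing and never mentions precision. Mixed models produce intervals, and whether to print them is commonly left to an analysis plan that is not shown. This stands in part: a reader might infer that intervals are ruled out, and the text does not say so. What remains is not silence, however. The paragraph states a rule on the point estimate and a rationale (in-sample, no inferential statements) that the rule itself breaks.

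**Compatibility with zero is conditional.** A reader might infer that 40 dyads cannot separate 0.3 SD from no change. The protocol gives no correlation and no SD of change, and at r = 0.7 the interval excludes zero. An estimate exactly at the mark is also the least favourable one that qualifies. If the true change were zero, one outcome at one visit would reach 0.3 SD about 2.9% of the time at n = 40 and 5.3% at n = 29 (r = 0.5, normal approximation). The 29-completer case is also a complete-case figure, whereas the plan is a mixed model under intention to treat. All of this stands, and the claim has to be that the estimate may be compatible with no change.

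**Nothing downstream turns on it.** A reader might infer that these effect sizes will size the randomized trial or decide whether it goes ahead. The documents do not support that. The progression section ties the decision to Table 5, which has no efficacy or 0.3 SD criterion. Table 5 and the Feasibility study outcomes section base the future sample size on baseline scores and variability, not on the observed change. The abstract and the Study aim section say only in general terms that the study informs the later design. This objection stands in full and limits the point to the efficacy statement.

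**Conclusion.** The point holds in a limited form. One paragraph disclaims inference, confines itself to in-sample effect sizes, and then gives a bare point estimate an efficacy label. At the 0.3 SD mark the 95% half-width ranges from 0.25 to 0.38 SD with 40 complete dyads, and from 0.30 to 0.45 SD with 29, for r from 0.7 down to 0.3. The estimate may therefore be compatible with no change: this needs r below about 0.56 at n = 40 or 0.69 at n = 29. Where zero is excluded at r = 0.7, the interval still runs from a small change to nearly double the estimate.

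These figures rest on an assumed correlation, equal SDs, complete pairs and an observed change exactly at the mark. They cover sampling error only. An interval would not allow a change to be attributed to the intervention, since "This study will employ a single-arm feasibility design without a control group".

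The choice of estimation, the sample size of 40 and the progression rules are not in question. Making the change is a cheap improvement.

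**What to change.** In the Quantitative analysis section, replace the sentence containing "Statistical power is not a primary concern as no inferential statements will be made" with wording to this effect: no hypothesis tests are performed; each effect size for change from baseline to 6 weeks and from baseline to 12 weeks is taken from the mixed model and reported with its two-sided 95% confidence interval; and any statement of potential efficacy quotes that interval and is read against it.

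The cost is one sentence. The planned models already supply the intervals, and no extra data, larger sample or design change is needed. The one downside is that some effects will look less certain than their point values suggest.

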#### Qualitative analysis

All qualitative interviews will be digitally recorded, transcribed verbatim by a professional transcription service, and uploaded into Dedoose (online software for qualitative data management) for analysis. A coding scheme and codebook will be developed, incorporating both externally generated codes based on the conceptual framework and internally generated codes emerging from the analysis. All codes will focus on identifying the challenges, acceptability and feasibility of the intervention, as well as opinions on session length, frequency, and delivery methods. Member checking will be conducted throughout the interview process. To enhance trustworthiness, an audit trail will be maintained, and the research team will regularly review and provide critical feedback on emerging codes. Analysis will involve examining patterns within and across coded texts to identify converging themes and reach consensus on key findings.

### Fidelity

Intervention adherence and fidelity will be assessed on an ongoing basis. Between 25–50% of the audio recordings of initial assessments and follow-up assessment meetings will be reviewed using the checklist [see Additional file 4]. This checklist provides a rating of the quality of the community health worker’s intervention delivery with regards to their core competencies, actions, and skills. The assessment and follow-up forms that correspond with the audio recordings will be reviewed for accuracy and completeness. The review will be guided by the intervention fidelity checkpoint lists and guides for addressing potential problems and offering appropriate solutions. A score of 35 and higher of the fidelity checklist assessment will be considered to meet fidelity requirements and adherence. All checklist scores and findings will be shared with the community health worker to improve intervention delivery and identify areas for improvement.

